### Study outcomes

The primary outcome measure is the proportion of patients with unfavorable neurological outcome at 180 days after randomization, assessed using the eGOS and dichotomized as “unfavorable” (eGOS 1–5) or “favorable” (eGOS 6–8). This scale has been largely used to assess neurological outcome in different interventional randomized trials dealing with acute brain-injured patients; mortality is part of the scale (eGOS 1).

Secondary outcome measures are (1) 28-day survival; (2) eGOS distribution between the two groups (i.e., ordinal outcome analysis); (3) ICU and hospital lengths of stay; (4) presence and severity of extra-cerebral organ dysfunction/failure, assessed using the daily Sequential Organ Failure Assessment (SOFA) score; (5) infection rate, except those involving only the central nervous system (CNS); (6) composite outcome (death and/or organ dysfunction/failure); (7) fluid balance; and (8) for centers monitoring brain tissue oxygenation (PbtO_2_), time spent with P_bt_O_2_ < 20 mmHg (brain hypoxic burden) will also be collected and analyzed, but reported into a separate secondary analysis.

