### Statistical methods: outcomes

Analysis of data is based on intention-to-treat. Statistical analysis will be performed using the last version of SPSS for Windows (Chicago, USA). Continuous variables will be summarized using medians and quartiles and analyzed using a Wilcoxon rank sum test. Categorical variables will be analyzed using the Fisher exact test. The primary outcome comparisons will be analyzed using a chi-square analysis and reported as an absolute risk reduction of poor outcome and its corresponding 95% confidence interval. The primary outcome will also be adjusted for pre-specified covariates (stratification criteria) and presented for each category of brain injury (TBI, SAH, ICH).

All secondary outcomes will be analyzed using independent samples *t*-tests, chi-square test, as appropriate, without additional adjustment. For 28-day mortality, the Cox proportional hazard model will be used to determine time-to-event hazard ratios and 95% confidence intervals.

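### Secondary outcomes fall under two incompatible test rules, and the promised ordinal analysis of the eGOS distribution is given no ordinal method

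*Protocol article*

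**What the plan says.** Three statements in the Protocol article bear on this.

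- *Statistical methods: outcomes*, first paragraph: "Continuous variables will be summarized using medians and quartiles and analyzed using a Wilcoxon rank sum test". The sentence after it reads: "Categorical variables will be analyzed using the Fisher exact test". Neither is limited to baseline or descriptive data.
- The same section, next paragraph: "All secondary outcomes will be analyzed using independent samples" t-tests or a chi-square test, "as appropriate, without additional adjustment". One outcome-specific method follows: "For 28-day mortality, the Cox proportional hazard model will be used".
- *Study outcomes* lists, as the second secondary outcome, "eGOS distribution between the two groups (i.e., ordinal outcome analysis"). Other items include "ICU and hospital lengths of stay", SOFA, infection rate, a composite of death and organ dysfunction, and fluid balance.

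No proportional-odds model, rank test or other ordinal method is named for the eGOS distribution.

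**The concern.** A reader who takes both paragraphs at face value has two tests for each secondary outcome other than 28-day mortality. For the continuous ones this matters, because the Wilcoxon test compares ranks and a t-test compares means. For skewed quantities the two can disagree, and the plan's summary by medians and quartiles matches only the first.

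For the eGOS distribution, the outcome list promises an analysis that uses the order of the grades, but the methods section does not deliver one. A chi-square test on a 2×8 table would give the same result if the grades were relabeled in any order. A t-test uses the order but gives the step from death (grade 1) to grade 2 the same weight as any other step, and it yields a mean difference in grade that is hard to interpret. What is at stake is the power and meaning of the analysis that should refine the dichotomized primary outcome.

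**Working it through.** **Which rule covers which outcome**

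| Secondary outcome | First paragraph | Second paragraph |
|---|---|---|
| Lengths of stay, SOFA, fluid balance | Wilcoxon | t-test |
| Infection rate, composite | Fisher | chi-square |
| eGOS distribution | Fisher if classed as categorical, Wilcoxon if classed as continuous | t-test or chi-square |
| 28-day survival | – | Cox model |

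The phrase on appropriateness can only choose between the two tests in its own sentence. Fisher's test on eight unordered categories ignores order just as the chi-square test does.

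**Planning figures, for context.** *Sample size* gives 50% versus 39%, 85% power, two-sided 0.05, 378 per group, and 397 per group after 5% loss. A two-proportion calculation gives 365 per group (pooled variance), 363 (unpooled) or 383 (continuity correction). Power at 378 per group is 86.2%. The total is 756 × 1.05 = 793.8, so 794. The stated size is close to these figures and has no bearing on this point.

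**Effect on the ordinal scale.** The planned shift as a common odds ratio for unfavorable outcome is (0.39/0.61) / (0.50/0.50) = 0.639, or 1/0.639 = 1.56 in the favorable direction.

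**Assumed control distributions for grades 1 to 8.** The protocol gives only 15% mortality and 50% in grades 1–5. The rest is assumed, in two versions:

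- A: 15/5/18/6/6/15/18/17%. Grades 1–5 sum to 15+5+18+6+6 = 50%.
- B: 15/5/15/7/8/15/15/20%. Grades 1–5 sum to 15+5+15+7+8 = 50%.

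Each cumulative odds is divided by 1.564. For grade 1: 0.15/0.85 = 0.1765; 0.1765/1.564 = 0.1128; 0.1128/1.1128 = 10.1%. For B the shifted distribution is 10.1/3.6/11.8/6.0/7.4/15.3/17.6/28.1%, and grades 1–5 sum to 39%, as planned.

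**Simulated power, two-sided 0.05.** A: 377 per arm (397 × 0.95), 3,000 trials. B: 378 per arm, 2,000 trials.

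| Test | A | B |
|---|---|---|
| 2×8 chi-square, 7 df | 71.2% | 72.0% |
| t-test on the grade | 92.4% | 93.5% |
| Wilcoxon rank sum | 93.1% | 94.0% |
| Dichotomized (1–5 vs 6–8) | 86.3% | 86.8% |

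The simulation error is at most about one percentage point: √(0.72 × 0.28 / 2000) = 0.010. The Wilcoxon row stands in for an unadjusted proportional-odds test, which is closely equivalent to it.

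The chi-square test falls about 22 points short of the rank test (93.1 − 71.2 = 21.9) and about 15 points short of the dichotomized comparison (86.3 − 71.2 = 15.1). The t-test is within one point of the rank test in both versions.

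**The case against.** The best defense is that the section moves from general defaults to specific rules. The primary outcome is categorical yet is assigned a chi-square test rather than Fisher's, so specific sentences seem to override general ones. On that reading the second paragraph governs secondary outcomes, and Wilcoxon and Fisher cover everything else. This is plausible and reduces the first part of the point to a clarification. It does not help the eGOS distribution, because it makes the t-test/chi-square rule binding there.

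A second defense is that calling the analysis ordinal, read with the phrase on appropriateness, rules out a chi-square test that ignores order, and that the exact model may sit in the statistical analysis plan. The first half is fair. It is also why the low power is not a certainty: with the t-test, power is nearly that of a rank test. But the article does more than stay silent. It names the permitted tests, and neither is an ordinal method.

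Three stronger readings are tempting and are not supported:

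- *Early deaths are counted as short stays.* The article says nothing on how deaths enter the length-of-stay comparison. A rule may exist in a document not shown.
- *The choice of test stays open until the data are seen.* An analysis plan may settle it, and *Statistical methods: additional analyses* assigns all analyses to an independent statistician.
- *The unadjusted analysis is wrong.* It is valid in a randomized comparison. Adjustment is an improvement, not the correction of an error.

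**Conclusion.** The point holds for the two conflicting test rules and for the missing ordinal method. If the eGOS distribution were tested by an eight-category chi-square, power would be about 71–72% against 93–94% for a rank or proportional-odds test, and below the 86–87% of the dichotomy it is meant to refine. If a t-test were used, little power would be lost, and the objection is to equal spacing of the grades and to the interpretation of the result.

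These figures rest on assumed eGOS distributions and a proportional-odds shift equal to the planned effect. The two versions agree within about one point. No size is put on the Wilcoxon/t-test or Fisher/chi-square conflict for the other outcomes.

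As a secondary remark only, the article states no rule for deaths in the length-of-stay comparison. If stays that end in death were compared as they stand, a mortality difference could show up as a difference in stay. The text does not say that this will be done.

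The primary analysis is unaffected. The change is worth making but is not critical.

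**What to change.** 1. Replace the blanket t-test/chi-square sentence with one test per secondary outcome, and say which variables the general Wilcoxon/Fisher sentences cover.
2. Analyze the eGOS distribution by proportional-odds regression adjusted for disease and GCS stratum as used at randomization. Report the common odds ratio with its 95% confidence interval. Show the full distribution by arm, so that readers can judge whether a single odds ratio describes it.
3. Use the Wilcoxon test for skewed continuous secondary outcomes such as SOFA and fluid balance, in line with the medians and quartiles already planned.
4. State how deaths are treated in the length-of-stay comparison. Time to discharge alive, with death as a competing event, is one option that uses recorded data.

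The cost is wording in the analysis plan; no new variable is needed. The adjusted model replaces the plan's explicit choice of no adjustment for secondary outcomes, so it should be recorded as a change. *Trial status* puts the end of data collection at June 2023, so at publication of the article this could still be settled before the final data were complete.

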### Sample size

The primary outcome measure of this study is the occurrence of unfavorable neurological outcome at 180 days, evaluated by a eGOS of 1–5. To calculate the sample size, we estimated a mortality rate of 15% and a percentage of poor neurological outcome of 35% (i.e., eGOS 1–5 of 50%). There are no specific epidemiological data to support this assumption, as the population is mixed (i.e., TBI, SAH, and ICH) and the proportion of patients being eligible for the study remains unknown. Thus, the initial sample size calculation identified a total of 2095 patients needed to be recruited for each arm to achieve a power of 90% at a two-sided alpha level of 0.05 or less to detect a reduction of poor outcome rate at 180 days from 50 to 45% (absolute reduction of 5%, i.e., 10% relative reduction) in one of the two arms. Sample size calculation was adjusted twice. The first change (approved in August 2019) consisted in considering a reduction in unfavorable neurological outcome rate at 180 days from 50 to 40% (absolute reduction of 10%, i.e., 20% relative reduction, *n* = 1000) in one of the two arms, considering the relatively low number of patients being eligible for the study. The second change (approved in June 2022) consisted in considering a reduction in unfavorable neurological outcome rate at 180 days from 50 to 39% (absolute reduction of 11%, i.e., 22% relative reduction, *n* = 756–378 patients per group) in one of the two arms, with a power of 85% and at a two-sided alpha level of 0.05. Considering a potential 5% lost to follow-up, a total of 794 patients (397 per group) are needed to complete the study. This last modification was decided because of the coronavirus disease 2019 (COVID-19) pandemic, which significantly disrupted recruitment and blood availability and led to uncertainty over future recruitment.

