## Methods: assignment of interventions

### Assignment of interventions: allocation

## Sequence generation

All eligible acute brain-injured patients during the study period in one of the participating centers can be considered for enrolment in the study. Randomization is performed using a computer-generated random sequence (variable blocks of 4, 6, and 8), stratified by center, by disease (TBI, SAH, or ICH), and by the Glasgow Coma Scale (GCS) at the moment of randomization (3–5; 6–9; 10–13).

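### The 28-day mortality Cox model is set to run without the disease and GCS strata used to randomize; including them is a small, free gain on a secondary outcome.

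*Protocol article*

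**What the plan says.** All references are to the protocol article.

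- **Sequence generation:** randomization is "stratified by center, by disease (TBI, SAH, or ICH), and by the Glasgow Coma Scale (GCS) at the moment of randomization". The GCS bands are 3–5, 6–9 and 10–13, and block sizes vary between 4, 6 and 8.
- **Study outcomes:** "Secondary outcome measures are (1) 28-day survival" opens the list of secondary outcomes.
- **Statistical methods: outcomes, primary outcome:** "The primary outcome will also be adjusted for pre-specified covariates (stratification criteria"), in addition to the chi-square comparison.
- **Same section, secondary outcomes:** all of them are tested by t-test or chi-square test "as appropriate, without additional adjustment".
- **Same section, next sentence:** "For 28-day mortality, the Cox proportional hazard model will be used", giving hazard ratios with 95% confidence intervals. It mentions no strata or covariates.
- **Discussion:** a remark on blood supply says the outcome assessment will be adjusted for the recruiting center. It names neither disease nor GCS, and it does not refer to the Cox model.

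**The concern.** Disease and GCS band are stratification factors and are recorded at randomization. The same section of the plan uses them for the primary outcome and then rules out adjustment for every secondary outcome. Read together, these sentences make the 28-day Cox model a two-group comparison that ignores how patients were allocated.

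Two things are at stake. If the strata are prognostic, a Cox model without them has less power than one with them. And if the arms differ by chance in their mix of disease or GCS, the unadjusted hazard ratio carries that difference. Deaths by day 28 may be few, so precision that costs nothing is worth having.

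**Working it through.** **The plan's own figure.** The document gives no number of events, hazard ratio or power for 28-day mortality. Its only calculation is for the primary outcome: 50% against 39%, "with a power of 85% and at a two-sided alpha level of 0.05", 378 per group. The pooled two-proportion formula gives (1.960·√(2·0.445·0.555) + 1.036·√(0.25 + 0.2379))² / 0.11² = 365 per group, or 383 with continuity correction. The stated 378 lies between these, and its power without correction is 86.2%. Then 756 × 1.05 = 794. This sets the size of the trial but says nothing about the mortality analysis.

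**Assumptions.** The 15% mortality in the Sample size section belongs to the 180-day outcome and is borrowed here; 25% is added as a higher case. Hazard ratio, strength of the strata and stratum shares are chosen for illustration.

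**Simulation 1.** N = 794, about 15% mortality, true HR 0.6 (log HR −0.511), 9 disease-by-GCS strata, censoring at day 28, 800 trials per scenario, each fitted with and without strata.

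| SD of stratum log hazard | Power, unadjusted | Power, stratified | Mean log HR, unadjusted | Mean log HR, stratified |
|---|---|---|---|---|
| 0.5 | 65.9% | 65.8% | −0.512 | −0.519 |
| 0.8 | 63.3% | 64.3% | −0.508 | −0.523 |
| 1.1 | 59.5% | 63.8% | −0.488 | −0.515 |

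The power difference is −0.1, 1.0 and 4.3 points.

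**Simulation 2.** N = 756, 1:1 allocation balanced within disease-by-GCS strata, true within-stratum HR 0.65, 3000 trials per scenario. Weak strata: hazard ratio 1.3 per GCS band, no disease effect. Moderate: 2.0 per band, disease step 1.5. Strong: 3.0 per band, disease step 1.5.

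| Control mortality (deaths) | Strata | HR, unadjusted | HR, stratified | Power, unadjusted | Power, stratified |
|---|---|---|---|---|---|
| 15% (about 95) | weak | 0.650 | 0.650 | 52.9% | 53.2% |
| 15% | moderate | 0.649 | 0.643 | 53.8% | 55.2% |
| 15% | strong | 0.658 | 0.645 | 52.0% | 55.2% |
| 25% (about 160) | weak | 0.652 | 0.652 | 75.3% | 75.9% |
| 25% | moderate | 0.656 | 0.645 | 75.2% | 77.8% |
| 25% | strong | 0.673 | 0.653 | 71.0% | 77.0% |

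The loss runs from 0.3 to 3.2 points at 15% and from 0.6 to 6.0 points at 25%. Entering disease and GCS as covariates gives nearly the same results as stratifying. As a check, Schoenfeld's formula with 95 deaths gives Φ(√95/2 · |ln 0.65| − 1.960) = Φ(0.14), about 55%, which agrees with the stratified fits.

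**Type I error.** With no treatment effect, the unadjusted test rejected in 3.6% of trials (15%, moderate strata) and 3.4% (25%, strong strata). The stratified test rejected in 4.2% and 5.1%. Ignoring the strata makes the test slightly conservative.

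**Chance imbalance.** Study setting gives 72 ICUs, so there are up to 72 × 3 × 3 = 648 cells for 794 patients, or 794/648 ≈ 1.2 per cell against a smallest block of 4. Simulating the stated block scheme with equal stratum shares and equal or unequal center sizes fills about 350–460 cells. The between-arm difference in the share of one GCS band then has a standard deviation of 2.5–2.9 percentage points. Under simple randomization it is √(2 · ⅓ · ⅔ / 397) = 3.3 points. In about 5% of trials the difference exceeds about 5 points. Stratified allocation therefore removes only part of the chance imbalance. Simulation 2 assumed balance within strata, so its results do not include this residual.

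**The case against.** **The text is not explicit.** The no-adjustment phrase closes a sentence about t-tests and chi-square tests, the Cox model follows in a sentence of its own, and a covariate list can be left to an analysis plan. This has some force. But the phrase governs all secondary outcomes, 28-day survival is one of them, and nothing in the Cox sentence makes an exception. The article states a choice here; it does not merely leave a detail open.

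**The hazard ratio is not biased.** This stands. A reader might infer that the planned model pulls the estimate wrongly toward 1. The unadjusted model estimates a marginal hazard ratio and the stratified model a within-stratum one; the gap between them is non-collapsibility. In simulation 1 the unadjusted mean log HR sits at the true value in two of three scenarios. A marginal estimate also matches the unadjusted absolute risk reduction planned for the primary outcome.

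**The gain may be nil.** This also stands: with weak strata the difference is within simulation error.

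**The remedy leaves out center, although the 648 cells arise from the centers.** True, but with about 95–160 deaths, stratifying the model by 72 centers would itself discard information. Disease and GCS are the practical factors, and they are the ones whose imbalance the remedy corrects.

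**Importance.** A reader might take 28-day survival for the main safety comparison. The article does not call it that. It lists the outcome first among the secondary ones and, under adverse event reporting, excludes death from the serious adverse events. Death also enters the primary outcome as eGOS 1, where adjustment is planned.

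**Conclusion.** The point holds as a minor one. As written, the 28-day Cox model omits disease and GCS band, while the same section uses them for the primary outcome. The analysis is valid for a marginal hazard ratio and its type I error is not inflated. The cost is about 0 to 4 points of power at about 15% mortality, and up to about 6 points at 25% mortality with strong strata, plus chance imbalance in disease and GCS left uncorrected. These sizes rest on assumed 28-day mortality, hazard ratios of 0.60 to 0.65 and assumed prognostic strength. The documents do not support describing the planned analysis as biased or invalid.

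**What to change.** In Statistical methods: outcomes, state that the Cox model for 28-day mortality is stratified by, or adjusted for, disease (TBI, SAH, ICH) and GCS band as randomized (3–5, 6–9, 10–13). Name the bands, because the subgroup section lists different ones (3–5, 6–8, 9–11). Exempt this outcome from the no-adjustment rule and report the unadjusted hazard ratio alongside, so the marginal estimate is kept. A model with a shared frailty for center is an optional sensitivity analysis.

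The cost is a line or two of text. Both factors are recorded at randomization, so no new data are needed and the sample size does not change.

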### Statistical methods: additional analyses

Subgroup analyses will be performed according to (a) underlying brain injury (TBI vs. SAH vs. ICH); (b) GCS at the moment of randomization (3–5; 6–8; 9–11); (c) presence of increased intracranial hypertension (defined as the need for specific therapies to reduce intracranial pressure [ICP]—if no ICP monitoring, then the patient is considered as not having intracranial hypertension); (d) age (< 45 years or ≥ 45 years); and (e) SOFA on randomization (< 8 and ≥ 8). Post hoc analyses will include (a) high- vs. middle- to low-income countries and (b) high-recruiting (i.e., > 25 patients) centers vs. others. All analyses will be processed by an independent statistician.

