## Methods: participants, interventions, and outcomes

### Study setting

This study will be conducted in 72 intensive care units (ICUs) worldwide. The complete list of recruiting sites is shown in Supplemental Table 1. The selection of participating ICUs was initiated within the Neuro-Intensive Care (NIC) Section of the European Society of Intensive Care Medicine (ESICM), with the identification of national investigators who then selected potential academic and non-academic ICUs with neurosurgical facilities and an adequate number of patients (> 50) with acute brain injury admitted per year. The study was initially expected to last 4 years, assuming the inclusion of 75–95 patients/month in 50–70 different centers. The final duration of the study will be almost 7 years, because of the slow recruitment rate, which is in part due to the recent pandemic crisis.

**Table 1 Tab1:** Inclusion and exclusion criteria of the TRAIN study

Inclusion criteria	Exclusion criteria
TBI, SAH, or ICH	Other neurological diseases, such as ischemic stroke or post-anoxic coma; status epilepticus without underlying brain injury; CNS infections (community-acquired; hospital-acquired; ventriculitis; post-operative)
Age ≥ 18 and ≤ 80 years	
GCS ≤ 13 on randomization	Known previous neurological disease, causing significant cognitive and/or motor handicap
Expected ICU stay > 72 h	ICH due to AVM or brain tumor
Hb ≤ 9 g/dL within 10 days from brain injury	Inability (religious reasons) or reduced ability (lack of compatible blood) to receive blood products
	Active and uncontrolled bleeding at the time of enrollment
	GCS of 3 with both pupils fixed and dilated; brain death or imminent death (within 24 h)
	Pregnancy
	Medical need to correct anemia (e.g., active coronary disease or severe cardiac disease) with target Hb levels > 9 g/dL
	DNE orders
	Previous allo-immunization due to transfusion, limiting RBC availability

*GCS*, Glasgow Coma Score; *ICU*, intensive care unit; *Hb*, hemoglobin; *DNE*, do-not-escalate (i.e., vasopressors, mechanical ventilation, renal replacement therapy); *CNS*, central nervous system; *ICH*, intracranial hemorrhage; *AVM*, arterio-venous malformation; *TBI*, traumatic brain injury; *SAH*, subarachnoid hemorrhage

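### The GCS subgroups stop at 11 although patients are eligible and stratified up to 13, and they put GCS 9 in a different band from its randomization stratum

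*Protocol article*

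**What the plan says.** Three places in the protocol article set ranges for GCS at randomization.

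- **Eligibility** (Table 1, under Study setting): "GCS ≤ 13 on randomization". At the lower end, the exclusion covers "GCS of 3 with both pupils fixed and dilated; brain death or imminent death (within 24 h"), so a score of 3 is not excluded as such.
- **Stratification** (Sequence generation): "Glasgow Coma Scale (GCS) at the moment of randomization (3–5; 6–9; 10–13").
- **Subgroups** (Statistical methods: additional analyses): "GCS at the moment of randomization (3–5; 6–8; 9–11").

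The strata are used again in the analysis. Statistical methods: outcomes states: "The primary outcome will also be adjusted for pre-specified covariates (stratification criteria").

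The article gives no reason for the different subgroup bands and no rule for patients scoring 12 or 13.

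**The concern.** The stratification and the subgroup analysis use one variable, measured at one time point, but cut it differently. The subgroup bands end two points below the protocol's own eligibility limit.

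If the text is followed as written, the mildest randomized patients are absent from the GCS subgroup analysis. The subgroups then do not add up to the randomized population, and any comparison of the treatment effect across GCS levels says nothing about scores 12 and 13. The same report would also carry two incompatible groupings of GCS, one for covariate adjustment and one for subgroups.

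Pre-specification suffers as well. The analyst will have to choose between leaving these patients out, stretching the last band to 13, or going back to the strata. If that choice is made once outcomes by arm are known, the subgroup analysis can no longer be called pre-specified.

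**Working it through.** No power or sample size formula bears on this point. The check is a score-by-score comparison of the stated bands.

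**Inputs**
- Eligible scores: 3 to 13, from Table 1 and the lowest stratum, which gives 13 − 3 + 1 = 11 values.
- Strata: 3–5, 6–9, 10–13 (Sequence generation).
- Subgroups: 3–5, 6–8, 9–11 (Statistical methods: additional analyses).
- Planned total: 794 (Sample size).

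**Mapping each eligible score**

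| GCS at randomization | Randomization stratum | Subgroup as written |
|---|---|---|
| 3, 4, 5 | 3–5 | 3–5 |
| 6, 7, 8 | 6–9 | 6–8 |
| 9 | 6–9 | 9–11 |
| 10, 11 | 10–13 | 9–11 |
| 12, 13 | 10–13 | none |

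**Results**
- Eligible scores without a stratum: none.
- Eligible scores without a subgroup: 12 and 13. That is 2 of 11 scores, and 2 of the 4 scores in the top stratum.
- GCS 9 is randomized in the middle stratum but analyzed in the top subgroup, so the 9–11 subgroup mixes one score from 6–9 with two from 10–13.
- Bands that agree: 3–5 only, so two of the three differ.

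**Patients affected (assumption, because no GCS distribution is given)**
- 5% with GCS 12–13: 0.05 × 794 ≈ 40.
- All 11 scores equally frequent: 2/11 = 18%, and 794 × 2/11 ≈ 144.
- 30% with GCS 12–13: 0.30 × 794 ≈ 238.

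**Possible corrections**
- Bands 3–5, 6–9, 10–13: each of the 11 scores falls in exactly one subgroup, and every subgroup is a stratum.
- Bands 3–5, 6–8, 9–13: all scores are covered, but GCS 9 still sits apart from its stratum.

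**Comparison with the other subgroups in the same section.** Disease (TBI, SAH, ICH), age (below 45, or 45 and over) and SOFA (below 8, or 8 and over) each place every patient. For intracranial hypertension there is even a rule for patients without ICP monitoring. Leaving patients out is therefore not how the article otherwise defines subgroups.

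**The case against.** The strongest reply is that this is a small slip in one of five listed subgroup analyses. The primary chi-square test uses no GCS bands, the adjusted analysis uses the complete strata, and sample size, alpha and the secondary outcomes are untouched. That is correct, and it limits how serious the point is.

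Subgroups also need not follow strata. A cut between 8 and 9 is not wrong in itself, and because GCS at randomization is a baseline variable, any banding of it gives a valid randomized comparison. This stands as a general principle. Taken alone, the GCS 9 discrepancy would only call for an explanation. It does not excuse bands that fail to cover the eligible range.

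The loss of stratified balance is small. With 72 ICUs, 3 diseases and 3 GCS bands there are 72 × 9 = 648 possible cells for 794 patients, about 1.2 per cell, with blocks of 4, 6 and 8. Many blocks would stay incomplete, so stratification guarantees little balance within a GCS band to begin with. This too stands, and the finding does not depend on it.

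Finally, the article names no treatment-by-GCS interaction test, does not say outright that patients scoring 12 or 13 will be dropped, and gives no basis for a patient count. The counts above are illustrations only. But dropping those patients is what the stated bands produce if applied as written, and nothing elsewhere in the article reconciles them.

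**Conclusion.** The concern holds. The subgroup definition contradicts both the eligibility limit and the randomization strata: GCS 12 and 13 have no subgroup, and GCS 9 changes band. This is a conflict between cut-points that the article itself states, so it is not a matter of detail left to an analysis plan.

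The firm size is 2 of 11 eligible scores. The number of patients is unknown; 40 to 238 of 794 rests on an assumed share of 5% to 30%. The consequence is an incomplete GCS subgroup analysis and an open choice of bands. The primary comparison and the stratum-adjusted analysis are unaffected. The coverage gap carries the finding; the shift of GCS 9 supports it, and the loss of balance adds little.

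**What to change.** In Statistical methods: additional analyses, replace the GCS subgroup bands with the randomization strata: 3–5, 6–9 and 10–13. Every eligible patient is then placed once, and the subgroups match the GCS covariate already used in the adjusted primary analysis. If a treatment-by-GCS interaction is estimated, use the same three levels.

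If the 8/9 cut was intended, the least that is needed is to extend the last band to 13 and state why it departs from the strata.

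Either way, record and date the correction before database lock and unblinding. The article reports 791 patients already recruited and an interim analysis already done by an independent statistician with access to the whole database, so the choice should be visibly made without knowledge of results by arm. The cost is one line of protocol or analysis plan wording. No new data are needed, because the score was required for randomization.
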